### Assessments to ensure internal validity

***Symptom severity at randomization.*** Symptom severity might change or fluctuate from the diagnostic interview or pre-assessment to the start of the intervention. In order to ensure clinically relevant transdiagnostic and disorder-specific symptomatology with the start of the intervention, scales that assess all primary and secondary outcomes will be presented again between randomization and group start: BSI-18 (Derogatis & Fitzpatrick, 2004), ISI (Dieck et al., 2018; Morin, 1993), PSQI(Buysse et al., 1989), PHQ-9 (Kroenke et al., 2001; Spitzer et al., 1999), GAD-7 (Lowe et al., 2008; Spitzer et al., 2006), PCL-5 (Kruger-Gottschalk et al., 2017).

**(Serious) Adverse Events.** Adverse events (AE) will be assessed at pre, post-1, and follow-up assessment. AEs and Serious Adverse events (SAEs) can be further reported by patients or therapists at a central phone number. AEs and SAEs will be documented and SAEs will be reported to an independent Data Safety and Monitoring Board, which will discuss adjustments to or discontinuation of the entire study**.**

**~~Treatment Fidelity (adherence to protocol of study therapists).~~** ~~Core elements of the manualized ImPuls intervention have been determined a priori. All inhouse sessions (see fig. 3 and table 1) of all therapists at all study sites will be video-taped despite outdoor MVAE. External research assistants will be trained to rate fidelity based on deliverance as intended in the manual. A treatment fidelity score will be determined as a mean of all ratings. 10 % of all video-taped sessions will be randomly selected and analyzed. A fidelity score of ≥ 90 % is assumed~~.

**Dropout and attendance rates (patients).** A drop-out rate less than 30 % and attendance rate ≥ 80 % is assumed. Attendance within the supervised (weeks 0-4; please refer to fig. 3) and partially supervised (weeks 5-24) period will be assessed via the ImPuls smartphone application and attendance lists by the exercise therapists/study site. Participants who miss more than 4 consecutive sessions during the four weeks of the supervised phase (of weeks 0-4) of the intervention (≥40%, due to any reason) but continue the study assessments are defined as treatment-dropout, since they did not receive the intended dose of the intervention. They can still participate in the remaining sessions of the intervention and will be asked to complete all remaining assessments. Participants who miss more than 4 consecutive sessions during the four weeks of the supervised phase (of weeks 0-4) of the intervention (≥40%, due to any reason) and discontinue the study assessments will be defined as study dropout. Participants who will discontinue the treatment as well as the assessments will be defined as study dropout. All participants agree to be asked to specify their reasons for study/treatment-dropout on a voluntary basis (once, after treatment/study dropout). If available, reasons for discontinuation will be reported. If more than 50% of participants will discontinue their participation in the intervention group during the first five weeks (weeks 0-4) of the delivery, discontinuation of the group due to lack of economic efficiency for the study sites is possible. If only one participant of the intervention group remains, he or she can no longer receive the intervention, since delivery of the intervention to less than two participants no longer qualifies as “group-based intervention”.

**MVAE dose within the supervised period (patients).** Frequency (at least twice a week), intensity (mean intensity of least 64 % of maximum heart rate) and duration (at least 30 minutes of MVAE in each session) of exercise during the supervised period (weeks 1-4) will be assessed via the ImPuls smartphone application.

**Expectations, Motivation and Satisfaction.** Validated scales adapted for use in the context of ImPuls will be employed to assess patients’ outcome expectations (Schulte, 2005), motivation (Schulz et al., 1995) and satisfaction with the intervention (Oei & Green, 2008), as well as exercise therapists’ motivation (Steinmayr & Spinath, 2010), and satisfaction with the intervention (Peters et al., 2002). On all scales, mean scores falling within the upper quartile will be judged as indicative of high motivation for and acceptability of treatment, respectively, in patients and exercise therapists.

**Process Evaluation.** ~~In addition to the goals related to investigating efficacy and cost-effectiveness of ImPuls reported in this study protocol, the overall project pursues additional goals focusing on process evaluation and implementation of ImPuls based on the Medical Research Council Guidance in the routine health care system, which will be described in a separate study protocol.~~

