Despite the promising evidence for MVAE as an intervention for patients with mental disorders, exercise programs or professional exercise therapy are currently not provided as regular health services within the outpatient mental health care system in Germany. With the aim of combining the current evidence on the efficacy of MVAE and sustained exercise behavior change with specific demands of a real-world outpatient health care setting, ImPuls was developed as a manualized group exercise intervention (Wolf et al., 2020; Zeibig et al., 2021) for physically inactive outpatients suffering from major depressive disorders, insomnia, panic disorder with or without agoraphobia and PTSD. ImPuls integrates recent findings about the optimal modalities of exercise for therapeutic efficacy, such as optimal frequency, intensity, time/duration and type of exercise (FITT criteria) for the targeted disorders and evidence regarding sustainable behavior change by integrating behavior change techniques (BCTs). The components of this intervention are further tailored towards the specific needs of outpatients with mental disorders in the current German mental health care setting. Specific features are 1) the inclusion of a broad range of heterogenous diagnoses for which prior research has demonstrated therapeutic efficacy, 2) intervention delivery in group format, and 3) short duration (i.e., only 4 weeks of supervised MVAE sessions carried out inhouse in each study site). The aim of the current study is to investigate the efficacy and cost-effectiveness of implementing ImPuls within the outpatient mental health care setting in Baden-Württemberg, a representative state in South-West Germany. The following hypotheses will be tested:

1. Participants in the intervention condition, who have received ImPuls in addition to TAU, will show lower global symptom severity at post-treatment and follow-up assessments compared to a control condition with TAU only.

2. Overall costs in the intervention condition will represent a significant saving for the public health system compared to the control condition at post-treatment and follow-up assessments.

3a. The intervention will lead to significantly higher levels of MVAE at post-treatment and follow-up assessments compared to the control condition.

3b. The effect of condition on the reduction of the primary outcome global symptom severity will be mediated by an increase in MVAE.

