# Interventions

*Item 11a: Interventions for each group with sufficient detail to allow replication, including how and when they will be administered.*

**ImPuls.** The exercise intervention “ImPuls” (Wolf et al., 2020) will be delivered to groups consisting of 6 patients and will be divided into a supervised and partially-supervised period. BCTs, such as goal setting, self-monitoring, formation of concrete exercise plans and coping planning, will be integrated to promote sustained exercise behaviour change (Abraham et al., 2009; Geidl et al., 2012; Michie et al., 2011). The intervention structure and contents are displayed in Figure 3 and Table 1. Participants will receive ImPuls in addition to TAU.

***Supervised Period (weeks 0-4).*** Patients will participate in a combination of supervised MVAE sessions and group sessions with educative elements integrating BCTs (see table 1) in groups with a total duration of 120 minutes each session. Supervised MVAE will be provided twice a week and will consist of either running or fast walking. MVAE will last 30 minutes and participants can choose between a standardized interval-based or endurance method protocol. Both training methods will be conducted with at least moderate intensity, which is tracked by a heart rate monitor (SIGMA iD.FREE) combined with a chest strap (SIGMA R1 Bluetooth Duo Comfortex+) and the Borg Rating of Perceived Exertion (RPE) Scale (Borg, 1982). Moderate to vigorous intensity is defined as at least 64 % of maximum heart rate, subtracting age from 220 (Garber et al., 2011) and at least 13 points of the RPE Scale (Borg, 1982). The ImPuls smartphone application (“ImPuls-App”) developed specifically for ImPuls supports the participants and therapists during MVAE. In weeks 2, 3 and 4 patients will engage in additional 30-minutes MVAE, which is chosen based on their own interests and preferences. Therapists provide a list of MVAE highlights in each study site (i.e. offers in local sport clubs, yoga studio, gyms) which can be found and selected in the “ImPuls-App”.

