All techniques/approaches will be delivered via the exercise therapists and protocoled, supported and guided by the ImPuls App.

*Item 11b Criteria for discontinuing or modifying allocated interventions for a given trial participant (eg, drug dose change in response to harms, participant request, or improving/worsening disease)*

Participants who miss more than 4 sessions in a row (of w0 to w4; supervised-phase) of the intervention (≥40%, due to any reason) but continue the study assessments are defined as **treatment-dropout**, since they did not receive the intended dose of the intervention. They can still participate in the remaining sessions of the intervention and will be asked to complete all remaining assessments. Participants who miss more than 4 sessions in a row (of w0 to w4; supervised-phase) of the intervention (≥40%, due to any reason) and discontinue the study assessments are defined as **study-dropout**. All participants agree to be asked to specify their reasons for study/treatment-dropout on a voluntary basis (once, after treatment/study-dropout). Reasons for discontinuation will be reported.

If more than 50% of participants discontinue their participation in the intervention group during the first five weeks (w0 to w4) of the delivery, discontinuation of the group due to lack of economic efficiency for the study sites is possible. If only one participant of the intervention group remains, he or she can no longer receive the intervention, since delivery of the intervention to less than two participants no longer qualifies as “group-based intervention”.  All participants, including drop-outs, will be asked to complete all of the following study assessments on a voluntary basis.

*Adherence*

*Item 11c: Strategies to improve adherence to intervention protocols, and any procedures for monitoring adherence (e.g., drug tablet return; laboratory tests).*

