**Intervention**

To ensure adequate delivery of the intervention, all exercise therapists were trained in the ImPuls program (see eligibility criteria). All exercise therapists are offered to take part in regular supervisions by a licensed exercise therapist or supervisor in cognitive-behavioral therapy, who are also trained in the ImPuls program by the study PI. All intervention sessions will be video-taped. 10% of the recorded sessions (randomly selected from pre-defined core-sessions) will be evaluated for treatment-fidelity by trained assessors. Every participant will set a 30-minute timer to monitor the duration of the supervised physical activity sessions. During the physical activity, intensity will be monitored through heart-rate monitors (w0-w4) as well as RPE (w0-w24). RPE will be assessed through automatic reminders of the smartphone application after 5, 15 and 25 minutes of physical activity.

The participants’ attendance will be monitored through the smartphone application as well as participation lists. If participants miss a session of the intervention, they will be asked to complete 30 minutes of moderate to vigorous physical activity on their own. They will be sent the material of the patient training session. All participants are asked to schedule and track their physical activity sessions performed during the supervised as well as unsupervised phase through the smartphone application. They will receive automatic reminders to perform the scheduled physical activity. Exercise therapists will be able to access these activity logs and monitor the physical activity after the supervised phase (w0-w4) through phone contacts. If participants fail to meet their goals, exercise therapists will revise the activity goals and measures to overcome obstacles with the participants. Frequency (at least twice a week), intensity (mean intensity of least 64 %) and duration (at least 30 Min each session) during the supervised period (4 weeks), will be assessed via the ImPuls smartphone application.

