To assess *fidelity*, we record all 10 inhouse sessions of each ImPuls group conducted by the exercise therapists (except outdoor running activity) on video. We will then randomly select one video for each group out of the eight core sessions to evaluate. This corresponds to 12,5% of all core sessions and 10% of all recorded sessions. Randomization is done by an independent person who creates a randomization list using the software R version 4.1.2 (R Core, 2021). We will develop separate rating forms for each ImPuls session. Research assistants of the evaluation team will rate the sessions with regard to adherence to the treatment manual and quality of delivery. Raters will be trained in understanding the ImPuls manual and central features (setting S.M.A.R.T. goals, implement coping plans, execution of 30 minutes of exercise, discussion about perceived exertion, planning of preferred individual exercise training plans). Adherence to the treatment manual is assessed by rating with “yes” (presence) or “no” (absence) as to whether pre-defined core elements of the ImPuls intervention are delivered. An overall inter-rater reliability score is calculated. Adherence is calculated according to the overall amount of “yes”/”no” answers of these items. Subsequently, the percentage of all items answered with “yes” is calculated in order to determine the final adherence percentage score. Quality of delivery is rated once per session on a 4-point Likert scale ([1] totally agree – [4] totally disagree) using four items (exercise therapist listens actively, allows breaks and periods of reflection to take place [tolerates silence], includes all participants, takes statements of participants seriously). A sum score is calculated.

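### The treatment-dropout rule equates missing more than 4 supervised sessions in a row with at least 40%, but with 10 in-house sessions that count is at least 50%

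*Protocol*

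**What the plan says.** The rule stands in two sections of the protocol. Under Interventions, Item 11b, it applies to participants who "miss more than 4 sessions in a row (of w0 to w4; supervised-phase) of the intervention (≥40%, due to any reason"). Under Assessments to ensure internal validity, in the paragraph on dropout and attendance rates, it applies to those who "miss more than 4 consecutive sessions during the four weeks of the supervised phase (of weeks 0-4) of the intervention (≥40"%). In each section the rule appears twice: for treatment-dropout (assessments continue) and for study-dropout (assessments stop). The second section adds a route to study-dropout that needs no session count.

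The denominator is given elsewhere. The fidelity paragraph under Qualitative Data says "we record all 10 inhouse sessions of each ImPuls group conducted by the exercise therapists", and the documentation paragraph under Quantitative Data ties the in-house sessions to the supervised phase. Item 11a says "Supervised MVAE will be provided twice a week and will consist of either running or fast walking".

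The expectation beside the rule is: "A drop-out rate less than 30 % and attendance rate ≥ 80 % is assumed".

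On the length of the phase, Item 11b describes a window "during the first five weeks (w0 to w4) of the delivery". The dropout paragraph calls weeks 0-4 four weeks in the rule and five weeks a few sentences later.

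**The concern.** The bracketed percentage is placed as the equivalent of the count, but the two differ by one session. Because 4/10 is exactly 40%, this looks like a slip between at least 4 and more than 4, and the text does not show which was meant.

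The rule is meant to identify patients who did not receive the intended dose. It helps decide who is reported as a dropout and asked for reasons, and treatment dropout is a listed process measure in Table 5. Two people applying the same sentence could report different rates beside the assumed figure below 30%. If the question stays open, the cut-off could be settled after attendance is known.

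**Working it through.** **Inputs.** Total supervised sessions T = 10 (Qualitative Data, fidelity paragraph). Cross-check: two sessions a week (Item 11a) over the five weeks w0 to w4 (Item 11b) gives 5 × 2 = 10. Count cut-off: more than 4. Percentage cut-off: ≥40%.

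**Does the count give the stated percentage?** The smallest whole number above 4 is 5, and 5/10 = 50%. The smallest k with k/10 ≥ 0.40 is 4, since 4/10 = 40%. The stated 40% is not reproduced, and a longest run of exactly 4 is classed differently.

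**Would another denominator reconcile them?**

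| T | 5/T | smallest k with k/T ≥ 40% | agree? |
|---|---|---|---|
| 8 | 62.5% | 4 | no |
| 9 | 55.6% | 4 | no |
| 10 | 50.0% | 4 | no |
| 11 | 45.5% | 5 | yes |
| 12 | 41.7% | 5 | yes |
| 13 | 38.5% | 6 | no |

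T = 8 is four weeks at two a week. T = 13 adds the three self-chosen sessions of weeks 2, 3 and 4. The protocol gives neither 11 nor 12 as a total for weeks 0-4. The supporters' session would make 11, but it falls in week 5, outside the rule's window.

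**How many patients could be affected?** Of the 2^10 = 1,024 attendance patterns over 10 sessions, 251 have a run of at least 4 misses and 112 a run of at least 5, so 251 − 112 = 139 are classed differently. To weight the patterns, assume the same mean miss probability q for everyone and a chance s of missing again after a miss. The chance of missing after attending is then q(1 − s)/(1 − q); for q = 0.2 and s = 0.7 this is 0.2 × 0.3/0.8 = 0.075. The base is 300 ImPuls patients (half of the target 600). Figures are patients meeting the session rule, whether or not they continue assessments.

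| Attendance | s | run ≥ 4 | run ≥ 5 | difference, of 300 |
|---|---|---|---|---|
| 80% | 0.2 (independent) | 0.9% | 0.2% | 2.3 |
| 80% | 0.5 | 9.9% | 4.4% | 16.7 |
| 80% | 0.7 | 19.1% | 12.0% | 21.1 |
| 80% | 0.8 | 22.4% | 16.4% | 18.0 |
| 80% | 0.9 | 23.2% | 19.7% | 10.7 |
| 70% | 0.3 (independent) | 4.2% | 1.1% | 9.3 |
| 70% | 0.5 | 14.9% | 6.6% | 24.9 |
| 70% | 0.7 | 28.4% | 18.0% | 31.2 |
| 70% | 0.8 | 33.4% | 24.6% | 26.5 |
| 70% | 0.9 | 34.8% | 29.5% | 15.8 |
| 70% | 0.95 | 33.4% | 30.5% | 8.5 |

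Differences come from unrounded probabilities. At 80% attendance neither reading reaches 30%. At 70% the readings fall on opposite sides of 30% only at s = 0.8 and 0.9.

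**Does it reach the sample size?** No. For d = 0.348, two-sided alpha 0.05 and 80% power, the t-test needs 130.6, so 131 per arm. Then 262/(1 − 0.30) = 374.3, rounded up to the stated 375. The session rule does not enter this calculation.

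**The case against.** The strongest reply is that the rule is the count and the percentage only a gloss. The count is worded the same way all four times, and every patient who meets it has missed at least 50% and so also satisfies at least 40%. On that reading nobody receives contradictory instructions; a patient with exactly four misses becomes a dropout only if the main clause is set aside. The bracket also does not repeat the consecutive condition, which suits a gloss better than a second rule. This stands, and it lowers the weight. It does not make 40% the right figure for the count.

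It is also fair that the reclassification figures rest on assumed clustering, for which the protocol gives no value, and that 70% attendance lies below what it expects.

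A reader might infer that five weeks is the only correct length throughout, so that the Introduction ("only 4 weeks of supervised MVAE sessions carried out inhouse in each study site") and Item 11c ("during the supervised period (4 weeks), will be assessed via the ImPuls smartphone application") are wrong too. The protocol does not support that. Both statements concern supervised exercise. The paragraph on exercise dose gives that period as weeks 1-4, the Participant Timeline notes define the supervised phase as weeks 1-4, and the therapist rules bar leave in weeks 1-4 but cover sickness in weeks 0-4. These point to a distinct week 0. Item 11a, with twice-weekly exercise under a heading of weeks 0-4, points the other way, and the program-structure figure is not available here. Only the dropout paragraph, which uses both lengths for the same weeks 0-4, is clearly inconsistent.

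**Conclusion.** The point holds as a minor error. With 10 in-house sessions, the count means at least 50% missed and the percentage means at least 4 sessions, so the operative rule carries a wrong threshold figure in both sections. This rests only on the protocol's own session total.

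The consequence is a dropout classification and rate that can differ between readers: about 2 to 21 of 300 patients at 80% attendance, conditional on the assumed clustering.

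A reader might infer that the efficacy result is at risk. It is not. Statistical Methods specifies intention to treat, the protocol defines no per-protocol set, and treatment-dropouts by definition continue their assessments. No decision is tied to the 30% figure, and the provision for stopping a group is worded in terms of discontinued participation, not this session count.

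**What to change.** State one threshold with its denominator, identically in Item 11b and in the dropout and attendance paragraph. Either of these is consistent:

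- *more than 4 of the 10 in-house sessions in a row (≥50%)*, which keeps the count as worded; or
- *at least 4 of the 10 in-house sessions in a row (≥40%)*, which keeps the percentage.

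In the dropout and attendance paragraph, use one length for weeks 0-4 in place of both four and five weeks; Item 11b already uses five for that window. Leave the four weeks of exercise in the Introduction and Item 11c unchanged.

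The cost is wording only, since attendance lists and app records are already collected. If at least 4 is chosen, the reported dropout rate will be somewhat higher. The choice should be made before attendance data are tabulated.

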## Quantitative Data

Exercise therapists, managers, and patients receive *online questionnaires* via the web-based data management system REDCap (Harris et al., 2019; Harris et al., 2009) at different time points (see Figure 3, Tables 2 (exercise therapists), 3 (managers), 4 (referring healthcare professionals), 5 (patients). All participants receive an individual web-link via E-mail to access the online survey and have 2 weeks to complete it (except weekly assessments during inter phases 1 - 2, where patients have only 1 week to complete it). Reminders are automatically sent out 5 days after receiving the survey invitation (for weekly assessments: 3 days). We primarily used existing and already validated (in German) measures. If these were not available in German, we translated them using established backward translation procedures utilizing native speakers. In order to gain a more profound insight into the processes of the ImPuls intervention, in some measurements of the exercise therapists, managers and physicians, we adapted the items specifically to ImPuls or developed items ourselves. Moreover, recruitment strategies allow for a variety of healthcare professionals (e.g., psychotherapists and primary care physicians) to refer patients to ImPuls. For this purpose, we ask them via online questionnaires about their opinion regarding exercise in combination with behavior change techniques as a new treatment option for patients with mental disorders.

Data of the *ImPuls smartphone application* is collected continuously during the supervised and partially supervised phase (inter 1 – 3; see figure 2 and table 5). It shows the extent to which patients use the ImPuls smartphone application (frequency) in general as well as regarding different application functions including goal setting, barrier management and training plans (patients‘ integration of core components). Repetitive negative thinking and valence of affect are measured with a self-developed self-assessment manikin prior to and after each supervised and unsupervised exercise session over the entire intervention period. We also collect data from the *web-based ImPuls interface* accompanying the ImPuls smartphone application to record the extent to which exercise therapists have used the tool to review patients’ shared information during supervised and partially-supervised phases.

We receive *documentation data* from the exercise therapists and from the project staff. Exercise therapists are required to document whether all scheduled inhouse sessions (supervised phase) and phone calls (partially supervised phase) were offered or completed. As part of the recruitment process, project staff document how patients became aware of the project, how patients are distributed among outpatient rehabilitative and medical care facilities and patient dropouts and their reasons before and during the study. Recruitment strategies include flyers and posters at the offices of the participating outpatient rehabilitative and medical care facilities, primary care physicians, psychotherapists and physiotherapists as well as a direct approach by health insurers involved in the project. We also disseminate information about the ImPuls intervention through self-help groups, daily newspapers, magazines, student mailing lists and social media.

